#### **A.4 METHODOLOGY**

Outline how you intend to achieve the objectives of the study.

*Guidance notes:*

*For each objective/hypothesis:-*

- *define the target population*
- *describe how the sample(s) is(are) to be recruited from the target population(s)*

*Even if the main thrust of the research is biomedical, the rationale behind your use of social science methods (e.g. patient interviews) should be clear.*

*describe how the sample(s) is(are) to be recruited from the target population(s)*

[figure not shown]

This will be a prospective randomized controlled trial of 2 arms.

- I. We intend to enroll a total of 320 HIV positive women delivering at MRRH. These will be equally randomized into the intervention arm (Family planning support) and control group (no family planning support, except the routine counseling following discharge). These women will be followed for 1 year. Eligibility will also require access to a mobile phone.

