In a superiority trial, one’s null hypothesis is that the two groups are equal and alternative hypothesis (or your main hypothesis) would be that one intervention is better (superior) than the other, in this case family planning support and availability. Two primary outcomes have therefore been suggested for this study; 1) Confirmed consistent use of an effective contraceptive method at 12 months and 2), pregnancy desire/aspirations among the HIV positive women. According to Nieves et al (2015), the rate of effective contraceptive use was found to be 45% amongst HIV positive women accessing HIV care at MRRH, although most of the contraceptive use was driven by condom use. Other studies have revealed that contraceptive prevalence would be 16 to 23 percent greater if all women lived in a cluster with the highest quality of care compared with the lowest one (Mensch et al., 1996). Another study also documented that the provision of the family planning voucher had a significant impact on contraceptive experimentation and long-term contraceptive use by an increase of 18 percentage points (Ashraf et al., 2014). We therefore hypothesize that improved family planning support and voucher will increase in effective contraceptive use among HIV positive postpartum women to at least 63%. This will therefore require a total of 156 women per group and an overall total of 312 HIV positive post partum women to have a 90% chance of detecting a significant increase at the 5% level.

For the second primary outcome, Nieves et al (2015) documents a pregnancy desire/aspiration rate of 33% for any HIV positive sexually active women attending ART clinic. Specifically, Snow et al (2014) also reported a lower and significant likelihood in desiring more children in future of 27.7% among married or cohabiting HIV-positive women when compared to 56.4% among HIV-negative women. Improved family planning accessibility and support offered through a voucher reduced the rate of births in the next year following the intervention to 6.8% (Ashraf et al., 2012). We therefore hypothesize a decrease in pregnancy or births in the next one year following our intervention to 6.8% with improved family planning availability and support among the recent post partum HIV-positive women. We shall therefore require a total of 80 women in each of the two groups and a total of 160 women in total to have a 95% chance of detecting a significant increase in pregnancy aspirations at the 5% level.

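### The sample size for the second primary outcome sets a pregnancy-desire rate against a birth rate, so the stated 95% power does not apply to pregnancy desire

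*Protocol*

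**What the plan says.** Protocol A.5.4 lists two primary outcomes. The first is confirmed consistent use of an effective contraceptive method at 12 months. The second is "pregnancy desire/aspirations among the HIV positive women".

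For the second outcome, A.5.4 gives these figures in order:

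- a baseline from one cited study: "a pregnancy desire/aspiration rate of 33% for any HIV positive sexually active women attending ART clinic";
- a baseline from another: "likelihood in desiring more children in future of 27.7% among married or cohabiting HIV-positive women", set beside 56.4% in HIV-negative women;
- a voucher study that "reduced the rate of births in the next year following the intervention to 6.8" per cent;
- the trial's hypothesis: "We therefore hypothesize a decrease in pregnancy or births in the next one year following our intervention to 6.8" per cent;
- the conclusion that 80 women per group, 160 in total, are needed "to have a 95% chance of detecting a significant increase in pregnancy aspirations at the 5% level".

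Elsewhere, A.4 plans 320 women randomized equally, and "These women will be followed for 1 year". A.3 lists pregnancy intentions (objective 1) and incidence of unintended pregnancy (objective 4) as separate objectives. Section 3.4.3 makes testing two-tailed with significance at p < 0.05.

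**The concern.** A two-group sample size needs the same variable in both groups. Here the baseline is the share of women who want a child, and the target is the share who give birth within a year. The gap between them (27.7% minus 6.8%, or 20.9 points) is not a treatment effect on either variable. Even with no intervention effect at all, the two rates could differ by that much.

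The paragraph also hypothesises a decrease and then claims power for an increase in aspirations.

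At stake is the reading of one of the two primary results. If desire shows no significant difference, a report citing 95% power would invite the conclusion that a worthwhile effect has been ruled out. The protocol's own figures do not support that reading.

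**Working it through.** **Inputs.** Baselines 33% and 27.7%, target 6.8%, power 95%, 5% level, 80 per group (all A.5.4); two-sided (3.4.3); equal allocation and 320 women, so 160 per arm (A.4). The calculation states no dropout allowance, and none is applied here.

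**Formulas**, per group, with d = p1 − p2, V = p1(1−p1) + p2(1−p2), and p̄ the mean of p1 and p2:

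- Unpooled: n = (z₀.₉₇₅ + z_power)² × V / d²
- Pooled: n = [z₀.₉₇₅ √(2p̄(1−p̄)) + z_power √V]² / d²

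**Step 1: check the formula on the first outcome.** For 45% vs 63% at 90% power, unpooled: 10.507 × (0.2475 + 0.2331) / 0.18² = 155.9. This is the protocol's 156.

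**Step 2: reproduce the 80.** For 95% power, (1.960 + 1.645)² = 12.995.

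| Control rate (desire) | Intervention rate (births) | Unpooled n | Pooled n |
|---|---|---|---|
| 27.7% | 6.8% | 12.995 × 0.2636 / 0.0437 = 78.4 | 81.9 |
| 33% | 6.8% | 12.995 × 0.2845 / 0.0686 = 53.9 | 57.3 |

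Rounded up, 27.7% gives 79 to 82 and 33% gives 54 to 58. The stated 80 fits the first row. The computation is sound; its two inputs belong to different outcomes.

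**Step 3: look for a matching pair.** A valid calculation on desire needs a desire rate under intervention. One on births needs a control birth rate. The protocol gives neither.

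**Step 4: what 160 per arm can detect on desire.** Power = Φ{[d√n − 1.960 √(2p̄(1−p̄))] / √V}, two-sided 5%, before dropout.

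Example, 27.7% to 13.2%: d√n = 0.145 × 12.649 = 1.834; 1.960 × √0.3254 = 1.118; √V = √0.3148 = 0.561. Then (1.834 − 1.118)/0.561 = 1.28, so power is 90%.

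| Control desire | 90% power needs a fall to | 80% power needs a fall to | Power for an assumed 10-point fall |
|---|---|---|---|
| 27.7% | about 13.2% | about 14.9% | about 57% |
| 33% | about 17.4% | about 19.3% | about 51% |

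**Step 5: spread over assumed desire rates under intervention**, 160 per arm:

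| Control desire | Falls to 10% | Falls to 15% | Falls to 20% |
|---|---|---|---|
| 27.7% | 98% | 79% | 36% |
| 33% | >99% | 97% | 75% |

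The rates under intervention in Step 5 and the 10-point fall in Step 4 are assumptions, not protocol figures.

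**The case against.** **The 80 does not set the trial's size.** This stands. The first outcome needs 156 per group, and 320 women are planned. A reader might infer that the trial is too small because of this error, but the documents do not support that. A.5.4 does say that enrolment and analyses run consecutively for the two primary outcomes. If that meant analysing desire on only 160 women, the 80 would matter: an assumed 10-point fall would then have about 33% power from 27.7% and 29% from 33%. The text does not say so.

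**Power for desire may be good.** It may be: from 33%, a fall to 15% has 97% power with 160 per arm. A reader might infer that power has been shown to be low. It has not; it is unknown, because no desire rate under intervention is given.

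**The 27.7% is a back-calculation.** It is, because the protocol does not say which baseline it used. Other pairs can give 80 (33% vs 10% does, pooled), but 10% appears nowhere in the protocol as a desire rate. Both stated baselines are desire rates, so the mismatch does not depend on the choice.

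**Increase versus decrease does not affect the number.** Correct under a two-tailed test. It is a wording contradiction and not a ground for rejecting the power figure.

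**Pregnancy or births could be the intended outcome.** A.3 separates pregnancy intentions from unintended pregnancy, and A.5.4 both declares desire as the outcome and ends on aspirations. Births would also need a control birth rate. A reader might go further and argue that a second birth within 12 months would have to be conceived before the intervention could act. The documents do not settle that. A.4 has a voucher given after delivery that expires 3 months after discharge, and also a 6-month initiation contact, while A.5.2 refers to 6 weeks. The stated hypothesis also covers pregnancy, which can be observed within the year.

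**Conclusion.** The point holds as an outcome mismatch, not as an arithmetic slip. The stated 80 per group at 95% power comes from a desire rate in controls set against a birth rate under intervention, and so is not a property of this trial for its declared second primary outcome. That follows from A.5.4 alone, whichever baseline was used.

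The consequence is a wrong power statement for one of two primary outcomes. Recruitment, randomization and the first outcome's calculation are untouched. The size of the gap depends on the effect assumed: with 160 per arm, 90% power requires a fall of roughly 15 points (27.7 − 13.2 = 14.5; 33 − 17.4 = 15.6), and the protocol offers no figure for how far desire would fall.

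**What to change.** Rewrite the second-outcome paragraph of A.5.4:

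- State the outcome as pregnancy desire at 12 months.
- Remove the 6.8% birth benchmark and the statement of 80 per group with 95% power from its calculation.
- Change increase to decrease, and name the control rate used.
- State the detectable difference for the planned size. For example: with 160 women per arm, two-sided 5%, before dropout, the trial has 90% power for a fall in desire from 27.7% to about 13.2% and 80% power for a fall to about 14.9%; from 33%, the corresponding rates are about 17.4% and 19.3%.
- Report pregnancies within 12 months separately under objective 4.

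The cost is one reworded paragraph and no extra women. The drawback is that the stated power for desire becomes less favourable than the present 95%.

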#### A.6 PROCEDURES

A.6.1 What procedures or methods will be employed in the collection of data (e.g. patient interviews / focus group discussions / blood sampling / biopsies) and by whom (e.g. experienced facilitator / social scientist / teacher/ qualified doctor / nurse, auxiliary, etc.)?

Attach additional sheets if necessary.

| Method             | To be carried out by:     |
|--------------------|---------------------------|
| Patient interviews | Nurse Research assistants |
| Observations       | Nurse Research assistants |
| Data entry         | Qualified data clerk      |

A.6.2 State the extent to which the procedures to be used are a part of usual clinical management (if appropriate).

- Family planning methods and proposed observations are routinely done to at post natal clinics 6 weeks following child birth.

A.6.3 Please indicate that the persons identified in A.6.1 are competent to carry out these procedures. List any training of staff that may be required prior to commencement of the study.

The project personnel will include highly qualified midwives/nurses to administer family planning methods, collect a blood sample for HIV testing/CD4 cell count and collect data. Highly specialised and qualified doctors at the ISS clinic will also review these mothers. A pharmacy technician will prepare the proposed treatments and a data clerk will double check and enter data.

## A.7 ANALYSIS

A.7.1 What are the major statistical (or other) methods that you intend to use to analyse the data to fulfil each of the objectives/hypothesis stated in A.3

### Data Preparation

All data will be cross checked for completeness before entry. Data will be coded and entered independently into the excel sheet and exported into STATA Version 12 for statistical analysis. For each variable, a reference category will be identified.

### 3.4.2 Data Analysis Plan

Data analysis will be by intention-to-treat (ITT) consisting of all mothers randomized and thus supposed to be treated (Lesaffre, 2008). Descriptive statistics will be used to describe key characteristics of study participants. Different variables will be explored for normal distribution. Selected demographic, clinical, post-natal factors will be compared for differences and similarities in the groups. We will compare dichotomous outcomes between study groups by estimating crude odds ratios with 95% confidence intervals, and testing for differences between groups with chi-squared testing and a level of significance of 0.05. Continuous outcomes will be compared using t-tests. A Mantel-Haenszel test will also be done to control for different variables. Crude relative risks will also be derived. Relative risks with 95% confidence Interval (two tailed) will be calculated and used to compare contraception effectiveness and pregnancy intentions in all groups. Factors associated with effective contraception use and pregnancy intentions will be explored using univariate analysis and for results whose p value  $\leq 0.10$ , a multivariate analysis will be done to rule out confounding factors.

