A different study nurse will be enrolled and trained to specifically collect data from participants. The socio-demographic data and obstetric characteristics will be documented. Other documented potential covariates of contraceptive use like participant age, primary partner's age, primary partner's HIV status, personal and partner fertility desires, number of children, most recent CD4 cell count, Efavirenz-containing ART Regimen (due to its association in decreasing levels of hormonal contraception thus recommending dual methods and its teratogenicity concerns-although these concerns have been found to be exaggerated), socio-economic status, body mass index, education level, time on ART . Prior contraceptive use experiences, fertility desire/ pregnancy intentions or aspiration will be measured using the CDC pregnancy Risk Assessment Monitoring System Instrument (Ahluwalia et al., 1999)

Effective contraception use will be defined as consistent use [both self report and observational chart review from study nurse at the family planning clinic] of a family planning method (including consistent condom use) , including dual contraception (use of condoms and another contraceptive method-hormonal or permanent) for HIV-sero discordant couples/partners (for participants who know partner's status). A primary partner will be defined either as a regular spouse, who is also a regular sexual partner or the most recent sexual partner if no main partner is named. These sexual partners will also be enrolled and interviewed at baseline and at 1 year. In case a consented mother ends up with a serious adverse event, the time and indication will be documented and reported. In case a woman changes the contraceptive method, the reasons for the change will also be documented.

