### 3.4.3 Data Reporting

The means will be presented with their standard deviations. Relative risks and odds ratios will be presented with their 95% confidence Intervals. Two-tailed statistical analysis will be used and statistical significance will be defined at level of  $p < 0.05$ .

[figure not shown]

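### The arms are compared by several crude and stratified analyses with none named as primary, although baseline pregnancy desire and prior contraceptive use could sharpen the comparison at almost no cost

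*Protocol*

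**What the plan says.** Section 3.4.2 of the protocol (Data Analysis Plan) sets out the between-arm analysis by intention to treat. Binary outcomes are handled thus: "We will compare dichotomous outcomes between study groups by estimating crude odds ratios with 95% confidence intervals". The accompanying test is chi-squared at the 5% level. Two further analyses follow: "A Mantel-Haenszel test will also be done to control for different variables" and "Crude relative risks will also be derived". The variables for the Mantel-Haenszel test are not named. Section 3.4.2 ties relative risks to both contraception and pregnancy intentions, and section 3.4.3 has both relative and odds ratios presented. Neither section says which result is primary.

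A separate sentence turns to predictors: "Factors associated with effective contraception use and pregnancy intentions will be explored using univariate analysis". Results with p ≤ 0.10 go forward, and "a multivariate analysis will be done to rule out confounding factors".

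On the data available, section A.4 (under Randomization) states: "Prior contraceptive use experiences, fertility desire/ pregnancy intentions or aspiration will be measured using the CDC pregnancy Risk Assessment Monitoring System Instrument". It also lists potential covariates of contraceptive use, including the woman's and her partner's fertility desires. Section A.4 schedules interviews at baseline, 6 and 12 months. Randomization is in blocks of 20, with no stratification factor stated.

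**The concern.** The protocol names likely prognostic variables, collects them, and plans a suitable method for using them. It does not connect the three. The comparison it fixes is crude, and the stratified one stands beside it with no variables and no rank.

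Two things are at stake. The first is precision: if a woman's desire or contraceptive history at baseline predicts her status at 12 months, a comparison stratified on it has more power from the same women. The second is the standing of the result: each primary outcome can yield a crude odds ratio, a crude relative risk and one or more Mantel-Haenszel results. If they fall on different sides of 0.05, nothing in the protocol says which counts. The scales also read differently. At 45% vs 63% the odds ratio is (0.63/0.37)/(0.45/0.55) = 2.08 and the relative risk is 0.63/0.45 = 1.40. Both describe the same effect, so this is no contradiction, but it is a reason to name one.

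**Working it through.** **Inputs from the protocol.** Section A.5.4: contraception 45% vs 63%, 156 per group, 90% power, 5% level; second outcome 27.7% vs 6.8%, 80 per group, 95% power. Section A.4: 320 women randomized equally, so 160 per arm. Section 3.4.3: two-tailed testing.

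**Inputs assumed.** The protocol gives no correlation between baseline variables and outcomes, so ranges are shown. Prior contraceptive use is taken as 45%, baseline desire as 30%, and the smaller-effect case for desire as 16% in the intervention arm. None of these three values is stated in the protocol for that purpose.

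**1. The plan's own figures.** n per arm = (z₁₋α/₂ + z₁₋β)² × [p₁(1−p₁) + p₂(1−p₂)] / (p₁−p₂)².
- Contraception: (1.960 + 1.282)² × (0.2475 + 0.2331) / 0.18² = 155.9, so 156. This is the stated figure.
- Second outcome: (1.960 + 1.645)² × (0.2003 + 0.0634) / 0.209² = 78.4, so 79 against 80 stated.

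Both are sized for a crude comparison.

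**2. Crude power at 160 per arm.** Power = Φ{[|p₁−p₂|√n − 1.960√(2p̄(1−p̄))] / √[p₁(1−p₁) + p₂(1−p₂)]}.
- Contraception: (2.277 − 1.381)/0.693 = 1.29, giving 90.2%.
- Second outcome: (2.644 − 1.047)/0.513 = 3.11, giving 99.9%.

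**3. Approximate gain from adjustment, contraception.** Multiply the variance by (1 − R²), so the effective n per arm is 160/(1 − R²). Power is 91.6% at R² = 0.05, 92.9% at 0.10 and 95.3% at 0.20. At R² = 0 there is no gain.

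**4. Simulation.** 60,000 trials per setting, one binary baseline variable with a constant odds ratio for the outcome, crude chi-squared test against Mantel-Haenszel. The correlation is that in the control arm. The last column is the type I error if success in either test counts.

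| Outcome | Correlation | Crude power | Stratified power | Type I error, either test |
|---|---|---|---|---|
| Contraception, 45% vs 63%, 160 per arm | 0 | 90% | 90% | 5.2% |
| | 0.17 | 90% | 91% | 5.8% |
| | 0.27 | 90% | 92% | 6.2% |
| | 0.33 | 90% | 93% | 6.5% |
| | 0.42 | 90% | 94% | 6.9% |
| Desire, 27.7% vs 16% (assumed), 156 per arm | 0 | 71% | 71% | 5.3% |
| | 0.30 | 72% | 74% | 6.5% |
| | 0.39 | 71% | 77% | 6.8% |
| | 0.49 | 71% | 80% | 7.3% |

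Each test alone kept type I error close to 5% throughout. The inflation comes only from allowing either to count.

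**The case against.** An unadjusted comparison of randomized arms is valid, and adjustment is optional. No stratification factor is stated, so the crude test ignores no design factor. It also delivers the planned 90% power before any loss to follow-up. All of this stands: a reader might infer that the crude analysis is biased or leaves the trial short of power, and the documents do not support that.

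A reader might also infer that the desire outcome is badly powered and depends on adjustment. At the stated rates its power exceeds 99%. The 71% arises only under the assumed 16%. Section A.5.4 does set a birth rate (6.8%) against a rate of desire (27.7%), so the true effect on desire is uncertain, but that makes a smaller effect possible rather than established. The larger gains also need strong correlations. With 30% baseline desire and a 6.8% outcome rate, the largest possible correlation is √[(0.068 × 0.70)/(0.30 × 0.932)] = 0.41. Section A.5.4 itself expects post-partum desire to be low, which would shrink the gain further.

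A third tempting reading is that the p ≤ 0.10 screen selects covariates for the treatment effect. Its sentence is about factors associated with the outcomes and most naturally serves specific objective 3 in section A.3. Only the remark about confounding leaves its reach unclear. In a one-covariate simulation, a test screened this way kept type I error at 4.8% to 5.1%.

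Finally, the choice of stratification variables and of a primary estimate is often left to an analysis plan, and one may exist. That would answer a complaint about silence. It does not fully answer this point, because the protocol itself commits to crude measures and sets an unranked alternative beside them. Nor does the protocol say that the better result will be picked; it simply does not rule it out.

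**Conclusion.** The point holds as an inexpensive improvement, not as an error that invalidates the analysis. For contraception, stratifying on prior use would raise power by about 1 to 4 points at assumed correlations of about 0.2 to 0.4 and would cost nothing at zero. For desire, the gain is negligible at the stated rates. It would be about 3 to 9 points at correlations of 0.3 to 0.5 if the intervention rate were 16%. The lack of ranking would matter most if the crude and stratified tests disagreed: accepting either would put type I error at about 6% to 7% at correlations of 0.3 to 0.5. The sizes rest on assumed prevalences and correlations, on one binary covariate per outcome, and on no missing data.

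**What to change.** In section 3.4.2, name one primary analysis per outcome: the Mantel-Haenszel risk ratio, with the risk difference and 95% confidence intervals. Stratify by baseline pregnancy desire for the desire outcome and by prior contraceptive use for the contraception outcome. Label the crude relative risk and crude odds ratio as supportive. Confirm that both stratifying variables are recorded at the baseline interview in both arms, and define their categories before outcome data are seen.

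Add one sentence stating that the p ≤ 0.10 screen belongs only to the exploratory factors analysis of objective 3 and does not choose covariates for the treatment comparison.

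The cost is a change of wording. The variables and the Mantel-Haenszel method are already planned, and no extra women, visits or measurements are needed.
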